## Abstract

**Background:**

Implementing efficient stoves and clean fuels in low and middle-income countries are critical for improving health of poor women and children and improve the environment. Cleaner biomass stoves, however, perform poorly against the World Health Organization’s indoor air quality guidelines. This has shifted the focus to systematic dissemination and implementation of cleaner cooking systems such as liquefied petroleum gas (LPG) among poor communities. Even when there is some uptake of LPG by poor communities, its sustained use has been low. Concurrent use of LPG with traditional biomass cookstoves compromises reductions in household air pollution and limits health and environmental dividends. Therefore understanding key drivers of adoption and sustained implementation of clean fuels among the poor is critical. There is a significant gap, however, in the research to understand determinants and sustained exclusive use of clean fuels in rural poor communities.

**Methods/design:**

Using a case control study design, this study will explore the impact of affordability, accessibility, and awareness on adoption and sustained use of LPG among rural poor communities of India. The study uses a multistage random sampling to collect primary data from 510 households. Case group or LPG adopters constitute 255 households while control group or non-LPG adopters constitute the remaining 255 households. The study will deploy sophisticated stove use monitoring sensors in each of the stoves in 100 case group households to monitor stove use and stacking behavior (using clean and traditional systems of cooking) of participants for 12 months. Moreover, this will be the first study to explore the impact of personal social networks striated by gender on LPG adoption. This study is guided by the RE-AIM (Reach, Effectiveness, Adoption, Implementation, and Maintenance) implementation science evaluation framework.

**Discussion:**

Lessons from this study will feed into a larger discussion on developing a pro-poor strategy to foster uptake and sustained use of cleaner cooking systems such as LPG. Understanding the determinants of adoption and sustained use of cleaner cooking systems through the RE-AIM framework will expand our insights on implementation of cleaner cooking systems among poor communities and will advance implementation science in the clean cooking sector. A thorough study of such implementation strategies is crucial to realize multiple UN Sustainable Development Goals on global health, climate change, and energy security.

## Background

### Challenges with cleaner biomass stoves

The UN commitment to achieving 17 global goals by 2030 includes “access to affordable, reliable, sustainable, and modern energy for all” (Global Goal 7). This goal recognizes the harmful impacts of household air pollution (HAP) on almost 41% of the global population, predominantly poor, who continue to rely on solid fuels such as biomass, crop residues, and dung, for heating and cooking [1]. Owing to poor combustion efficiency, these solid fuels release aerosol emissions and particulate matters. They are a major source of HAP. These emissions have a detrimental impact on health, climate, and environment. Particularly, poor women and children are at a high risk of exposure to biomass smoke and adverse health outcomes causing acute and chronic respiratory infection [2]. Approximately 4.3 million annual premature deaths are attributed to HAP exposure [3]. Nearly 50% deaths from acute lower respiratory infection among children below 5 years in underdeveloped countries are attributed to exposure to HAP [3]. Continuous exposure to these emissions also leads to pregnancy complications and stunted growth of children [3]. In 2013, slightly more than 900,000 deaths have been attributed to HAP in India [4, 5].

Adoption and sustained use of cleaner cooking technologies such as cleaner biomass stoves or cleaner fuels (Liquefied Petroleum Gas [LPG]) are recommended as solutions to address the challenge of HAP. Dissemination and implementation (D&I) in the clean cooking sector has most recently focused on cleaner biomass stoves [6–9] . Strategies to disseminate and implement these cleaner biomass stoves among poor communities are motivated by four realizations: 1) a supra-linear nature of the HAP exposure-response curve suggests that expected health benefits of clean cooking can be attained only at very low levels of exposure [10, 11]. This means that health benefits can be derived only when biomass stoves reduce emissions from combustion to extremely low levels. However, most of the cleaner biomass stoves in use or being developed perform poorly against the World Health Organization’s (WHO) recommended indoor air quality guidelines (IAQG). Exposure levels with these cleaner biomass stoves during routine use in households are far higher than the recommended IAQG. Therefore health related benefits are not as forthcoming despite switching to cleaner biomass stoves; 2) communities have to continue to perpetually depend on biomass as a cooking fuel to use cleaner biomass stoves. These stoves do not offer a sustainable solution in terms of degradation of forests due to continued biomass harvest for use in these stoves for cooking and heating [8]; 3) drudgery of collecting biomass and associated physical injuries continue to pose health and economic challenges. Poor community members (especially women) have to travel long distances to collect biomass. Injuries from carrying heavy logs of wood and biomass are common among women in rural communities; 4) most of the cleaner biomass stoves developed in laboratories have poor performance in terms of robustness and mechanical wear and tear in real world conditions. Thus, despite some promise offered by these cleaner biomass stoves, health and environmental benefits are substantially compromised. It is increasingly recognized that while efforts are required to develop standards and technology for cleaner biomass burning, more emphasis is needed to deploy cleaner cooking systems such as LPG.

### Previous research on adoption and sustained use of LPG: Key limitations

Available literature on LPG use by poor communities can be broadly analyzed along supply and demand side of LPG.

#### Supply of LPG for poor households

Studies on LPG from the supply point of view have mostly focused on subsidies, pro-poor financing techniques, and low cost supply chain to increase affordability of LPG adoption and use for poor households. LPG, a clean and modern household fuel is a petroleum product and its price is mostly governed by fluctuations in international markets [12]. Nevertheless, it continues to outpace increase in income of poor communities [6, 12]. Blanket fuel subsidies provided by governments such as India reduce direct costs of acquiring LPG by households. However, such subsidies have not been successful as a policy instrument to increasing supply in poor communities. Poor households account for only a small part of total LPG fuel use as compared to their wealthy counterparts [8, 9, 13]. Supply of clean fuels such as LPG to billions of poor communities requires high-level policy initiatives. It involves careful trade negotiations and a mechanism of differential subsidies [8, 9]. Streamlining subsidies of LPG to benefit poor communities is a gradual process [14] involving multiple stakeholders (petroleum companies, petroleum rich nations, and national government subsidies) with conflicting interests [15]. It may also require an overhauling of energy policy at a higher level [12]. Large-scale studies of the supply of LPG are significant to address the challenge. Streamlining of subsidies, low cost supply chain mechanisms, and pro-poor financing techniques have the potential to make LPG more affordable for poor households [15]. However, even if the government attains an enabling supply-side climate, uptake and sustained use of LPG remains a distant goal if there is a limited demand from poor communities. Smith and Sagar [8] and Slaski and Thurber [16] argue that commensurate demand may expedite both rationalization of subsidies and revamp of energy policy for poor communities. A stronger evidence base on how to stimulate LPG demand among poor is needed [8, 12, 13, 17, 18].

#### Demand of LPG by poor households

There are limited and scattered studies focusing on analyzing the demand of LPG by poor households and most of the studies have combined different cleaner cooking technologies (including LPG). There has been growing attention to exploring causality between affordability of households and adoption of LPG. For instance, the majority of the empirical literature on adoption of cleaner cooking systems (including LPG) have three variables in common in their analyses: 1) household size; 2) income; and 3) fuelwood price [19]. The relationship between income and adoption is moderated by social class, gender, acquisition barriers, and ethnicity. Female-headed households with higher incomes are more likely to adopt cleaner cooking technologies. In patriarchal societies even if the households have higher income, they are less likely to adopt LPG [20]. Households belonging to marginalized groups, lower castes,^1^lower social class, or indigenous groups are less likely to adopt LPG [19].

Existing literature on adoption and sustained use of LPG by poor communities has three limitations. They are: 1) LPG is not a primary fuel in a majority of poor communities. Stacking clean fuels with traditional cooking technologies is common, which limits expected health and environmental dividends [21]. Limited systematic studies are available to explore this challenge of stacking and many do not account for stacking in a methodical way; 2) successful cases of poor households who have sustainably used LPG are needed. Lessons from such cases can then be adapted and tailored for other poor communities; 3) there is considerable attention to understanding the impact of affordability on LPG use. Increase in affordability to purchase LPG may drive uptake and sustained use. Lewis, Bhojvaid [22] argue that even if the acquisition barriers (like upfront cost) are waived to make cleaner technologies more affordable, sustained and exclusive use is low. Increase in affordability is a significant, however, an inadequate driver. Limited accessibility and awareness restrains communities from transition to and sustained use of LPG [16, 23, 24]. There is limited evidence exploring combined issues of affordability, accessibility, and awareness (3As) and their relation to adoption and sustained use of LPG by poor communities [25, 26].

## Methods

### Study aim

This paper is part of our larger study aimed at exploring the determinants of adoption and sustained use of LPG in resource poor communities of rural India. The study is guided by the RE-AIM (Reach, Effectiveness, Adoption, Implementation, and Maintenance) implementation sciences framework. This protocol paper highlights the application of the RE-AIM framework in our study of LPG implementation in poor households. The overarching goal of our study is to derive new insights on the reach of LPG among the poor in rural India, factors that influence adoption (initial uptake), sustained use, and maintenance of LPG in below poverty line (BPL) households in rural India. Our specific aims are:To understand how below poverty LPG adopters vary from other BPL households on factors of affordability, accessibility, and awareness of LPG.To determine how affordability, accessibility, and awareness affect sustained and exclusive use of LPG in adopter households.To evaluate the relative influence of gender networks on LPG adoption and sustained use in BPL households.

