**Fig. 1 Fig1:**
[figure not shown]
Impact of 3As on adoption and sustained use of LPG. This figure is a visual representation of the conceptual model arguing the concurrent role of affordability, accessibility, and awareness in fostering adoption and sustained use of LPG in poor communities. This study will test the validity of this model

Different stove adoption related studies have defined adoption and use in ways specific to their studies. It is imperative to define the five concepts illustrated in Fig. 1. Definitions of these concepts as they pertain to this study are:
*Awareness* refers to the degree of knowledge and perception about LPG adoption and use [19]. Several studies recognize the significance of awareness in motivating households for a fuel switch [19, 22]. Scattered evidence suggests that low information and scattered rumors on LPG safety issues may act as a deterrent to uptake and use of LPG by these rural households [23]. Measures of affordability, accessibility, and awareness are predictors of outcome variables of adoption (aim 1) and sustained use (aim 2) in this study. To further explore impact of awareness, we will also conduct social network analysis (aim 3) to assess how knowledge and awareness flows through social networks and consequently impacts the decision to adopt LPG among households.
*Accessibility* of LPG indicates factors impacting a household’s ability to procure LPG cylinders and stoves when needed. Factors affecting accessibility include (but are not limited to) distance to rural LPG distribution center, delivery mechanism of LPG cylinders, and road connectivity from villages to local distribution centers [23].
*Affordability* refers to the maximum possible capacity of households to pay for the minimum level of services [23]. Affordability is impacted by household factors such as income and LPG demand, and also by government policies on LPG subsidies [23].
*Adoption* refers to the initial uptake of LPG [29, 30]. Adoption of LPG is independent of the behavioral phenomena of sustained use of LPG or stacking LPG with traditional stoves. Adoption of LPG is a dichotomous outcome variable (LPG adopter households/LPG non adopter households) in this study (aim 1).

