
The RE-AIM framework emphasizes multilevel and concurrent examination of household and organizational level factors driving adoption, implementation, and maintenance of health interventions, instead of an isolated examination of such levels [33, 34, 36]. It seeks to address the ‘voltage drop’ as interventions move from efficacy testing to real world sustainment [37]. The barriers and enablers of adoption and use occur at individual and possibly at organizational levels. The study protocol allows us to examine both these levels [34]. Similarly, individual and organizational level factors may influence effectiveness of an intervention [34, 36]. While affordability is a household level factor, accessibility and awareness of LPG cut across household and organizational level factors. RE-AIM framework allows us to examine how affordability, accessibility, and awareness at multiple levels influence adoption and sustained use of LPG [33, 34, 36] in study aim 1 and study aim 2. In addition, gender networks in communities also influence uptake and use of health interventions [38]. Aim 3 explores the relative influence of personal gender networks of males and females in selected households and their impact on LPG adoption. Figure 2 synthesizes the placement of the three aims and analyses of our study within the RE-AIM framework.

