#### Aim 2: To determine how affordability, accessibility, and awareness affect sustained use of LPG in adopter households

To study sustained use, we will focus on group 1 (LPG adopters) of our sample. SUMS will be used to measure duration of use (a measure of maintenance) of clean cooking technologies of the study participants. We will use SUMS for both the LPG stoves and traditional cookstoves in a randomly selected subset of 100 households from group 1 (LPG adopters) [31]. We will receive SUMS data on: 1) duration of use of these stoves; 2) extent of use of LPG stoves relative to traditional stoves. We will monitor the use of these stoves for 12 months. SUMS data will be recorded and downloaded every two weeks from each of the 100 households by a trained field person. We will download data using a probe connected to a laptop computer via USB port. Files will be uploaded to our database management system (RedCap). Informed consent will be obtained from the households to continue using the stoves as they do routinely. SUMS will provide continuous data on stove usage in 100 households. For analysis purposes, we will also dichotomize this data as: 1) exclusive LPG users, and 2) stackers. Households using LPG at least 80% of the cooking duration during the monitoring period of 12 months will be characterized as exclusive LPG users. This metric will facilitate comparison of the results of this study with other LPG adoption studies currently underway in different parts of the world [32]. We will use a SUMS data log sheet to record the biweekly SUMS data on sustained use. In addition, we will undertake a follow up survey in these 100 households. During the monitoring period (post enrollment of households) status of 3As in the habitations might change. This requires a follow up survey at the end of 6 and 12 months of the monitoring period. Follow up survey will have questions pertaining to the 3As, focused on the monitoring period. Follow up questionnaires and SUMS data collection will be administered to 100 LPG adopter households.

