#### Aim 3: To evaluate the relative influence of gender networks on LPG adoption in rural households

Personal social networks of individuals in communities influence awareness levels, which in turn drive adoption, implementation, and maintenance of stoves [39]. Implementation of health interventions are impacted by the personal networks of men and women in the households [38, 39]. Both men and women play a critical role in adopting, implementing, and maintaining cleaner cooking technologies like LPG [39]. Thus, it is critical to assess the personal networks of study participants to ascertain how they influence (or get influenced by) decisions related to making a fuel switch. To generate personal network data, we will use a personal network survey to probe the women (primary cook) and the adult male (or primary male decision maker) of 100 households each in the case and control groups. This approach is novel in understanding the role of gender dimensions and the peer effects impacting their fuel choice. Personal social networks, or egocentric networks, focus on the structure and composition of the networks surrounding a target individual [40]. We will use a well-established ego-centric network survey instrument to measure personal networks of men and women. The gendered network data will be collected as follows: 1) the survey will begin with three name generator questions to prompt identification of individuals who give advice, socialize, and support the respondent. 2) After eliciting the network members, a second set of questions will be performed to evaluate the strength of the connections (tie strength) between the respondent and the individuals identified by the respondent; 3) subsequently, the strength of the connections between the network members identified will be probed; 4) finally, characteristics of the network members identified will be solicited (e.g., their demographics, income, household size, and cooking habits).

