### Research instruments

A summary of the research instruments is provided in Table 2. Each of the research instruments will be drafted in English and will be translated into Telugu (local language of the region in India).

**Table 2 Tab2:** Data collection instruments

Conceptual domains	Aims	Research instrument	Method or Measure	Data source	Sample size
Adoption of LPG	Aim 1	Adoption questionnaire	Structured interview	Households: women	LPG adopter households (case): 255; Non-LPG adopter households (control): 255
Sustained use of LPG	Aim 2	SUMS	Stove temperature monitoring	Households: LPG and traditional stoves	LPG adopter households (case): 100
Sustained use of LPG	Aim 2	Follow up questionnaire	Structured interview	Households: women	LPG adopter households (case): 100
Personal social networks of LPG adopters and non-LPG adopters impacting adoption of LPG	Aim 3	Social network survey questionnaires for women and men	Structured interview	Households: women, men	LPG adopter households (case): 100 Non-LPG adopter households (control): 100

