## Discussion

In this study we bring three novel approaches together to gain new insights:Apply the RE-AIM (Reach, Effectiveness, Adoption, Implementation, and Maintenance) framework to explore LPG adoption and use. RE-AIM framework will guide this research and development of measures for reach, adoption, implementation, and maintenance in the clean cooking sector.Delineate adoption and sustained use as separate outcomes and analyze them as a function of affordability, accessibility, and awareness (3As) of LPG.Deploy Social Network Analysis (SNA) to understand how gender networks matter in dissemination of awareness and consequently in adoption of LPG.

In combining these approaches, we will be able to: 1) examine the pooled impact of the 3As on LPG adoption and sustained use, absent in the present stock of research; 2) assess the relative influence of personal gender networks of men and women on the adoption and sustained use of LPG, contributing to our understanding of the role of gender networks in the implementation of clean cooking, 3) understand these effects through the RE-AIM framework to apply our insights toward implementation of cleaner fuels and advance implementation science in the clean cooking sector. This will be the first systematic study to use personal social networks striated by gender to analyze LPG adoption in rural India. Lessons drawn from this study are timely, relevant, and of interest to Government of India’s renewed focus on policy design (including provisions in annual budget 2016) and implementation to expand LPG distribution to the poor in rural India [8, 9, 44]. The Government of India (GOI) has committed to redesigning their LPG policy and distribution to penetrate rural communities using a combination of direct cash transfer programs (PAHAL), campaigns encouraging non-poor to give up LPG subsidies (GiveItUp campaign), and smaller LPG cylinders [9]. Systematic research is needed to undertake a concurrent analysis of the 3As and their corresponding impact on both adoption and sustained use of LPG in rural hosueholds. Careful assessment of the elements of 3As could facilitate a model of a succesful pro-poor strategy for LPG uptake and sustained use.

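### Aim 3 promises to relate gender networks to sustained LPG use, but only adoption is analysed, and the article does not say whether the network-survey and SUMS adopter households coincide

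*Protocol article*

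**What the plan says.** Two places in the article give aim 3 two outcomes. The list of specific aims (Methods, Study aim) has "To evaluate the relative influence of gender networks on LPG adoption and sustained use in BPL households". The Discussion says the study will be able to "assess the relative influence of personal gender networks of men and women on the adoption and sustained use of LPG".

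The sections that put the aim into practice name one outcome:

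- The definition of awareness (Study design, under Fig. 1) says the social network analysis will show how knowledge flows through networks and "consequently impacts the decision to adopt LPG among households".
- The RE-AIM section says "Aim 3 explores the relative influence of personal gender networks of males and females in selected households and their impact on LPG adoption". It assigns maintenance, the RE-AIM term for sustained use, to aim 2.
- The aim 3 headings under both Data collection and Data analysis read "To evaluate the relative influence of gender networks on LPG adoption in rural households".
- Table 2 gives the conceptual domain of the network survey as "Personal social networks of LPG adopters and non-LPG adopters impacting adoption of LPG".

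On the samples, SUMS are placed "in a randomly selected subset of 100 households from group 1 (LPG adopters"), while the network survey is given to the women and men "of 100 households each in the case and control groups". Table 2 lists 100 adopter households for SUMS, for the follow-up questionnaire and for the network survey, without saying how the three sets relate.

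**The concern.** A specific aim needs an outcome, a sample that carries both exposure and outcome, and an analysis that joins them. The adoption half of aim 3 has all three. For the sustained-use half, the outcome is measured under another aim, the sample with both measures is undefined, and no joining analysis is described. If the plan is followed as written, the study ends with a stated aim half answered, or with an unplanned analysis fitted afterwards to whichever households happen to have both kinds of data.

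The question of which households are used also depends on timing. Twelve months of stove monitoring cannot be recreated later for network-survey households that never had sensors.

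**Working it through.** **Step 1: is there an analysis that links networks to sustained use?**

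| Section | Outcome | Network data used? |
|---|---|---|
| Study aim, aim 3 | adoption and sustained use | promised |
| Discussion | adoption and sustained use | promised |
| Awareness definition | adoption | yes |
| RE-AIM section | adoption | yes |
| Data collection, aim 3 | adoption | yes |
| Table 2, aim 3 row | adoption | yes |
| Data analysis, aim 3 | adopter v. non-adopter | yes |
| Data analysis, aim 2 | exclusive user v. stacker | no; predictors are the 3As |

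The aim 3 analysis looks at structural holes, density and composition across case and control groups, and names no SUMS or exclusive-use outcome. The first aim 2 analysis is a usage trend without covariates. The second regresses the exclusive-user indicator on the 3As from the follow-up questionnaire. No row joins network data to sustained use.

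**Step 2: can the adoption contrast stand in?** No. The article defines adoption as initial uptake and treats it as separate from later use or stacking. Sustained use is measured only within adopters, so a comparison of adopters with non-adopters carries no information on which adopters keep using LPG.

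**Step 3: the plan's own sample-size figure.** The only comparison that is sized is monthly income: difference 545.35 INR, SD 2199.26 INR, two-sided alpha 0.05, power 80%.

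n per group = 2 × (1.960 + 0.842)² × (2199.26 / 545.35)² ≈ 255.3, rounded up to 256.

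With 255 per group the power is 0.7995, so the stated figure reproduces. It has no bearing on aim 3, for which no sample-size calculation is given.

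**Step 4: how many adopter households would have both measures?** Inputs: 255 adopters, 100 with SUMS, 100 in the network survey.

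- If the two sets are the same: 100.
- If they are two independent simple random draws (an assumption; the article gives no selection method for the network set), the overlap is hypergeometric. Mean = 100 × 100 / 255 = 39.2. Variance = 39.2 × (155/255) × (155/254) ≈ 14.5, so SD ≈ 3.8. The 95% range is 32 to 47.
- Other selection methods could give fewer.

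**Step 5: what the difference would mean.** Standard errors with 39.2 households rather than 100 are larger by √(100/39.2) = 1.60. As an illustration, take exclusive users to be 20% to 50% of households (an assumption; the article gives no figure). The standardized difference in a network measure between exclusive users and stackers that is detectable with 80% power at two-sided 0.05 is (1.960 + 0.842) × √(1/n₁ + 1/n₂):

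| Households with both measures | 20% exclusive | 50% exclusive |
|---|---|---|
| 100 | 0.70 SD (20 v. 80) | 0.56 SD (50 v. 50) |
| 39 | 1.11 SD (8 v. 31) | 0.90 SD (20 v. 19) |

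**The case against.** The strongest reply has three parts.

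First, a reader might infer from the separate descriptions that the SUMS and network households are different. The article does not say so. Both sets number 100 adopter households, and the same 100 could serve SUMS, the follow-up questionnaire and the network survey. A condensed article may also leave the allocation of instruments to the full protocol. This part stands: silence about the overlap is not a fault in itself, and the figure of 39 describes one assumed scenario, not the plan. The overlap matters here only because a stated aim depends on it.

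Second, a reader might conclude that the sustained-use question cannot be answered at all. That is also too strong. If the households coincide, the data will exist. What is missing is a described analysis that uses them.

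Third, the study calls itself exploratory, and the working sections make an adoption-only scope fairly clear. Even the Discussion elsewhere ties networks to adoption alone. This suggests that the error may lie in two sentences and not in the design, and it makes narrowing the aim a reasonable remedy. It does not remove the contradiction: an exploratory study still has to say which outcomes its specific aims address.

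**Conclusion.** The point holds as an internal contradiction. The list of aims and the Discussion promise the influence of gender networks on adoption and sustained use. The sections that carry out aim 3 deliver adoption only, and the aim 2 regression has no network variable. This conclusion rests on the text alone and needs no assumption.

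The size of the data problem is uncertain. The number of adopter households with both measures is 100 if the sets coincide and about 39 (32 to 47) under independent random draws, and the article does not say which applies. Even with 100, precision is modest: on the assumed 20% to 50% share of exclusive users, only differences of roughly 0.56 to 0.70 SD are detectable with 80% power. The article's own Limitations section already calls 100 households small for the sustained-use regression.

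**What to change.** Choose one of two changes.

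1. **Keep the wider aim.** State in the aim 3 data collection section that the 100 adopter households in the network survey are the 100 SUMS households. Add to the data analysis section an exploratory analysis relating a small number of male and female network measures, chosen in advance, to SUMS-measured LPG use. Keep the number small: with an assumed 20 to 50 exclusive users among 100 households, a long list of network predictors on top of the 3As would overfit. Label the result exploratory and report intervals. The cost is one sentence on sampling, one on analysis, and more survey load on the same households; the planned number of interviews does not change. Settle this before the households are selected, or, if sensors are already placed, before the network survey starts.

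2. **Narrow the aim.** Delete the reference to sustained use from aim 3 in the Study aim section and from the matching sentence in the Discussion. This costs two text edits and gives up a question for which no analysis is at present described.
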